### Sample size

Sample size computation is based on the changes in cerebral vascular hemodynamic parameter between comparison groups with a 5% per comparison significance level and a two-tailed critical region. The mean and SD of cerebral vascular hemodynamic parameter in the control group as obtained from relevant literature are 32.0 and 6.0 respectively [37]. We expect a 10% mean improvement of this outcome after 12-week *Baduanjin* exercise intervention. A total of 170 participants is calculated as needed to detect the target effect size with 90% power. In order to avoid excessive loss to follow-up, we will illustrate in detail to the participants the potential health benefits of *Baduanjin* exercise. For completeness of whole trial progress we will also provide confidence incentives to participants. Furthermore, we will collect information from participants in both the *Baduanjin* exercise and the usual physical activity control group regarding the likelihood that they will drop out. This information will be used to attempt to reduce the incidence of drop-out.

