### Primary outcomes

Cerebrovascular function consists of cerebral vascular hemodynamic and cerebrovascular elasticity. Cerebral vascular hemodynamic parameters consist of the maximum blood flow velocity (Vmax), minimum blood flow velocity (Vmin) and mean blood flow velocity (Vmean). Those parameters from the vertebral, basilar, middle cerebral, anterior cerebral and posterior cerebral arterial territories of the brain will be measured using Color Doppler ultrasound imaging device (PHILIPS, product type: IU22) by the professional operators at the Affiliated Rehabilitation Hospital of Fujian University of Traditional Chinese Medicine. Cerebrovascular elasticity consists of the elasticity index (PI) and vascular resistance index (RI) of vertebral, basilar, middle cerebral, anterior cerebral and posterior cerebral arteries. It will be measured using Color Doppler ultrasound imaging device (PHILIPS, product type: IU22) by the professional operators at the Affiliated Rehabilitation Hospital of Fujian University of Traditional Chinese Medicine.

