### Statistical analysis

Statistical analyses will be performed using SPSS 21.0 (IBM, Chicago, IL, USA) software packages by a statistician, who is not involved in the outcome measurements, at Center of Evidence Based medicine, Fujian University of Traditional Chinese Medicine. The statistical significance is defined as two-sided *P* value of < 0.05. In descriptive analysis of the sample, the central tendency for the continuous variables will be expressed using mean (standard deviation) or median (interquartile range) for symmetrical distributions; normality will be tested using the Kolmogorov-Smirnov test. Appropriate transformations will be applied in cases of a non-normal distribution. The categorical variables will be expressed as proportions with their standard error. Statistical comparisons for the baseline characteristics, primary and secondary outcomes between groups will be compared using the Student’s *t-*test or Mann-Whitney *U*-test for continuous variables and the Pearson Chi-squared or Fisher exact test for categorical variables. Analysis of the primary and secondary outcomes will be on the basis of the intention-to-treat (ITT) population and per-protocol (PP) population. The result of the ITT analysis will be compared with that of the PP analysis to determine whether the results are consistent. Every effort will be made to minimize missing data and drop-out or loss to follow-up during the study period. Missing data will be filled by Bayesian methods. If the amount of missing data for primary outcome or potential confounders is substantial (that is > 10%), multiple imputation methods will be considered to perform the statistic analysis. Linear models or linear regression will be applied for dependent continuous variables and logistic regression models for dependent categorical variables if incomparability of baseline characteristics between groups appears. Subgroup analysis stratified by participants’ sex will be used for the primary outcomes. Analysis of variance (ANOVA) will be used for the repeated measurement data, and the *post hoc* comparison will be applied if the difference is found to be significant. Adverse events will be listed and analyzed using a Chi-squared or Fisher’s exact test. Severe adverse events will be listed in detail.

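### A sex subgroup described only as stratified, with two-group tests named, does not test whether the effect differs by sex and invites a false claim that it does

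*Protocol article*

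**What the plan says.** The Statistical analysis section gives the subgroup one sentence: "Subgroup analysis stratified by participants"' "sex will be used for the primary outcomes". It names no test for this analysis and does not say how a difference between men and women would be judged.

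The surrounding text supplies the available methods:

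- For between-group comparisons: "Statistical comparisons for the baseline characteristics, primary and secondary outcomes between groups will be compared using the Student" t-test or the Mann-Whitney test when the variable is continuous.
- One threshold, with no separate level for subgroups: "The statistical significance is defined as two-sided" P below 0.05.
- Linear or logistic models, but only "if incomparability of baseline characteristics between groups appears".
- ANOVA for repeated measurements, with no mention of sex as a factor.

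The Sample size section is for the trial as a whole, "with a 5% per comparison significance level and a two-tailed critical region". The control mean and SD "as obtained from relevant literature are 32.0 and 6.0 respectively", the expected improvement is 10%, and 170 participants are planned for 90% power. The inclusion criteria admit both sexes without stating an expected split.

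**The concern.** Neither the t-test nor the Mann-Whitney test can carry a group-by-sex term. If the subgroup analysis uses the tests named, it becomes the same two-group comparison run once in men and once in women, each judged at 0.05.

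A significant result in one sex and not in the other is not evidence that the effect differs. Each stratum has only part of the sample and so less power than the whole trial. When the true effect is the same in both sexes, one test will often reach 0.05 while the other misses it by chance. A reader of such a result could conclude that the exercise helps only men or only women. That would be a false statement about a difference, and it could discourage a prevention measure in a group that benefits from it.

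**Working it through.** **Inputs from the protocol article.** Control mean 32.0 and SD 6.0; improvement 10%, so the effect is 0.10 × 32.0 = 3.2; two-sided alpha 0.05; 1:1 allocation with 85 per arm.

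**Assumptions.** The sex split is not given, so a range is shown, equal in both arms. SD and true effect are the same in both sexes, everyone is analysed, and a single outcome is considered.

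**The plan's own figure first.** n per arm = 2 × (1.96 + 1.2816)² × 6.0² / 3.2² = 73.9, so 74 per arm and 148 in total, against 170 stated. With 85 per arm the power is 93.5%. The total of 170 is therefore not reproduced without an unstated allowance, such as dropout of roughly 12% to 13%: 148/0.88 is 169 and 148/0.87 is 171 after rounding up. That is a separate matter. The calculation below uses 85 per arm as planned.

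**Power within one sex.** With m participants of that sex per arm, SE = 6.0 × √(2/m) and power ≈ Φ(3.2/SE − 1.96). At 50:50, m = 42.5, SE = 1.302, 3.2/1.302 = 2.458, and power = Φ(0.498) = 69.1%. The noncentral t gives 68.1%.

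**Chance that exactly one sex is significant.** Men and women are different people, so the two tests are independent and P = p₁(1 − p₂) + p₂(1 − p₁). At 50:50 this is 2 × 0.691 × 0.309 = 42.7% (normal) or 2 × 0.681 × 0.319 = 43.4% (t).

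| Split | m per arm | Power, normal | Exactly one, normal | Exactly one, t |
|---|---|---|---|---|
| 50:50 | 42.5 / 42.5 | 69% / 69% | 43% | 43% |
| 60:40 | 51 / 34 | 77% / 59% | 45% | 46% |
| 70:30 | 59.5 / 25.5 | 83% / 48% | 51% | 52% |
| 80:20 | 68 / 17 | 88% / 34% | 62% | 63% |

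**Sensitivity.** With 74 per arm analysed, the normal figures run from 47% (50:50) to 63% (80:20). At 50:50 with 85 per arm, other equal true effects give 36% (effect 1.6), 50% (2.4) and 23% (4.0). With no effect in either sex it is 2 × 0.05 × 0.95 = 9.5%.

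**Comparison with an interaction test.** A simulation of 40,000 trials per split, with the effect equal in both sexes, gave one-sex-only significance in 43.4%, 45.8% and 51.6% of trials for 43/42, 34/51 and 26/59 per arm. An interaction test at 0.05 rejected in 4.8%, 4.9% and 5.1%. At 43/42, both happened together in 4.6%, so only about one in ten of the discordant results (4.6/43.4) came with a significant interaction.

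**Precision of the interaction.** At 50:50, SE = 6.0 × √(4/42.5) = 1.84, so the 95% CI is ± 1.96 × 1.84 = ± 3.6. Power to detect a difference of 3.2 between the sexes' effects is Φ(3.2/1.84 − 1.96) = 41%.

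**The case against.** The strongest objection is that the premise is inferred. The article does not announce separate tests, a comparison of P values or any sex-specific conclusion. Showing stratum results beside an interaction test is ordinary practice, and an article may leave such detail to the full protocol or analysis plan. A repeated-measures ANOVA is also named and could in principle include sex. All of this stands. A reader might infer that the plan prescribes separate tests; the text does not go that far. The absence of an interaction test from the article is not the point either. The point is that the method it does commit to, read with the tests it names, answers the wrong question.

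Three further readings are tempting and are not supported:

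- *The trial is likely to report a benefit that is only noise.* In the scenario behind the 43%, the benefit is real in both sexes; only the apparent difference is false. At splits from 50:50 to 60:40 the chance is below one half. The figure is also the chance of discordant P values, not of the authors making a claim.
- *The many primary parameters and territories make this a subgroup problem of its own.* The Primary outcomes section does list them ("Those parameters from the vertebral, basilar, middle cerebral, anterior cerebral and posterior cerebral arterial territories of the brain will be measured"), but that multiplicity affects the main comparison equally, and interaction tests would carry it too. It is a separate issue.
- *An interaction test would settle the question.* It would not: its 95% CI of ±3.6 is wider than the design effect of 3.2. Its merit is that it holds the false-difference rate near 5% and shows the uncertainty openly.

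In the plan's favour, only one subgroup factor is named, it is limited to the primary outcomes, and the main intention-to-treat comparison is untouched.

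**Conclusion.** The point holds as a weakness in how the sex subgroup is specified. On its natural reading, the stated method does not test whether the effect differs by sex. Under an equal effect of the size the trial was designed for, it would give significance in exactly one sex in about 43% of trials at 50:50, 45% to 46% at 60:40 and about 52% at 70:30, against about 5% false differences with an interaction test.

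These figures rest on the within-sex reading, an assumed sex split, the protocol's SD and effect, and one outcome with everyone analysed. The conclusion that one-sex-only significance would be common is not sensitive to the split. It weakens if the true effect is much larger than planned (23% at 4.0). The main treatment comparison is not affected.

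**What to change.** Replace the subgroup sentence with wording such as:

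> For each primary parameter analysed, a difference in effect between men and women will be assessed by a group-by-sex interaction term in a linear model, fitted whether or not baseline characteristics are balanced. The effect in each sex will be reported with its 95% CI, together with the interaction estimate, its 95% CI and P value. This analysis is exploratory, and no sex-specific conclusion will be drawn from within-sex P values.

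The cost is small: a few lines of text, no new data and no change to sample size. Two consequences should be accepted. A linear model must be fitted for this purpose, whereas the current text keeps such models for baseline imbalance. And the interaction will be estimated imprecisely (SE about 1.84 at 50:50, 41% power for a difference of 3.2), so a non-significant interaction must not be read as proof that the sexes respond alike.

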### Intervention

#### Baduanjin exercise group

The participants in the *Baduanjin* exercise group will receive a 12-week *Baduanjin* exercise training with a frequency of five days per week and 40 minutes per day. Eighty-five participants will be freely gathered into three training units with 25 to 30 people per training unit, and the *Baduanjin* exercise training will be performed at Wufeng Community Center. We will employ three professional coaches, who have engaged in teaching the college students physical education at the Fujian University of Traditional Chinese Medicine for at least five years, to guide participants’ training. The training scheme of *Baduanjin* exercise originated from the ‘*Health Qigong Baduanjin Standard’* enacted by the State Sports General Administration in 2003 [38]. The whole set of Baduanjin exercise consists of ten postures (including the preparation and ending posture) (Figure 2) [39]. Two supervisors will be in charge of the management of each training site to guarantee the quality of Baduanjin exercise training.

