### Usual physical activity group

Participants allocated to the control group will not receive any specific exercise training from the study scheme. They will be requested to maintain their original habit of physical activity.

In order to exclude bias from the exceed activity of participants, all participants in both groups will be required to record an activity log in the intervention period, in which the duration and intensity of their activity or exercise in a whole day will be classified into three sections including the duration of low-intensity activity, the duration of moderate-intensity activity, and duration of high-intensity activities.

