### Safety

Although no adverse event from *Baduanjin* exercise is reported to this day, all unexpected adverse events during the intervention period will be reported to the project manager, and the causality with *Baduanjin* exercise intervention will be analyzed. If serious adverse events do occur, they will be reported to the primary researchers and ethics committee immediately and they will decide whether the participant needs to withdraw from this trial.

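### The planned adverse-event test may compare detection as well as harm, because in weeks 1 to 12 only the exercise arm has regular staff contact

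*Protocol article*

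**What the plan says.** For adverse events, the Statistical analysis section of the protocol article says "Adverse events will be listed and analyzed using a Chi-squared" or Fisher exact test, with severe events listed in detail. The threshold is set once for the whole analysis: "The statistical significance is defined as two-sided" P below 0.05. The sentence on adverse events does not say that the arms are compared, but the same section names these two tests for comparing categorical variables between groups, and a two-arm trial offers no other natural use for them.

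The exercise arm trains for 12 weeks "with a frequency of five days per week and 40 minutes per day" under three coaches, and "Two supervisors will be in charge of the management of each training site" (Baduanjin exercise group). For the other arm, "Participants allocated to the control group will not receive any specific exercise training from the study scheme" and "They will be requested to maintain their original habit of physical activity" (Usual physical activity group). Both arms keep an activity log, described as the time spent in low, moderate and high intensity activity.

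The Safety section has unexpected events in the intervention period reported to the project manager, with "the causality with" the exercise assessed. Table 1 marks adverse-event recording for weeks 1 to 12 and 13 to 24 without limiting it to one arm. Under Follow-up, supervisors telephone every two weeks about the quality of the log. Both arms are assessed at weeks 13 and 25.

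**The concern.** A test of two proportions compares harm only if an event has the same chance of being recorded in either arm. For the first 12 weeks the article describes very different opportunities. An exercise participant who falls, feels dizzy or has a sore knee is in front of staff on most weekdays. A control participant with the same complaint has no scheduled contact and a form that, as described, has no place for it. The Blinding section adds that participants and coaches know the allocation.

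The participants are 50 to 70 years old with several vascular risk factors, so background events are plausible in both arms, and the control arm is there to supply that background. If its events are recorded less completely, the exercise could appear to cause harm that it does not cause, or a real reduction in events could be hidden. Once the data are collected, no analysis can separate the two, because the observed rate is the product of risk and detection.

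**Working it through.** **Contact as described**

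| Period | Exercise arm | Control arm |
|---|---|---|
| Weeks 1 to 12 | 5 days × 12 weeks = 60 scheduled staffed sessions, plus activity log | activity log |
| Weeks 13 to 24 | 12 / 2 = about 6 calls on log quality, plus activity log | the same |
| Weeks 13 and 25 | outcome visit | the same |

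The imbalance is confined to weeks 1 to 12. The 60 sessions are the schedule; the Discussion allows self-practice at home in bad weather.

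**What unequal detection would do to the test**

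The document gives no adverse-event risk, no detection probability and no power for adverse events, so there is no stated figure to reproduce. What follows is an illustration.

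- From the document: 170 participants allocated 1:1, so 85 per arm; two-sided 0.05; chi-squared or Fisher exact test.
- Assumed: the same true risk π in both arms; detection 90% in the exercise arm; detection 90%, 70% or 50% in controls.

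The observed rates are p₁ = 0.90π and p₀ = d₀π. For example, π = 20% and d₀ = 50% give p₁ = 0.18 and p₀ = 0.10, that is 85 × 0.18 = 15.3 against 85 × 0.10 = 8.5 participants expected with a recorded event.

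With a and b such participants in the two arms, the Pearson statistic for 85 per arm reduces to X² = 170(a − b)² / [(a + b)(170 − a − b)], and the test rejects when X² exceeds 3.841. Fisher rejects when its two-sided P is below 0.05. The false rejection rate is the sum, over all pairs (a, b) that reject, of Bin(a; 85, p₁) × Bin(b; 85, p₀). It was computed by full enumeration.

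| True risk, both arms | Detection, exercise v control | Chi-squared | Fisher |
|---|---|---|---|
| 10% | 90% v 90% | 4.9% | 2.8% |
| 20% | 90% v 90% | 5.1% | 3.1% |
| 30% | 90% v 90% | 5.1% | 3.4% |
| 10% | 90% v 70% | 7.3% | 4.4% |
| 20% | 90% v 70% | 10.9% | 7.5% |
| 30% | 90% v 70% | 15.2% | 11.4% |
| 10% | 90% v 50% | 16.2% | 10.6% |
| 20% | 90% v 50% | 32.3% | 25.5% |
| 30% | 90% v 50% | 49.5% | 41.6% |

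With rare events and 90% v 50% detection:

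| True risk, both arms | Chi-squared | Fisher |
|---|---|---|
| 2% | 3.1% | 0.2% |
| 3% | 6.2% | 0.9% |
| 5% | 9.3% | 3.3% |

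With equal detection both tests hold their level. The inflation comes entirely from the detection gap, and it grows with the gap and with the number of events.

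**The case against.** The strongest reply is that unequal contact is not the same as unequal recording. Table 1 marks adverse events for recording in both periods without distinguishing arms, and the Safety section covers all unexpected events in the intervention period. How events are elicited is the kind of detail a journal article leaves to the full protocol, which may well set one enquiry for everyone. From week 13 on, calls and visits are the same in both arms. The only statement on frequency is that no adverse event from Baduanjin has been reported; if events are rare, Fisher, which the plan names, stays below its nominal level even with 90% v 50% detection. No primary or secondary outcome depends on this test, and events are listed as well.

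Most of this stands, and it rules out some stronger readings. A reader might infer that the tests themselves are biased. They are standard for proportions; any bias would enter through data collection, and another test would not remove it. A reader might also infer that control events are under-counted and that no valid background rate will exist. That is a risk, not something the document shows. Nor is assessing causality against the only study intervention an error.

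What remains is that the article commits to a formal test and describes the contact on which events from weeks 1 to 12 would rest, and that contact is unequal. The equal calls start after the imbalance ends and are described as log checks. The rare-event argument also concerns events caused by the exercise, whereas the test would count background events too.

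**Conclusion.** The point holds as a caution about interpretation and a cheap improvement, not as a demonstrated bias. Run on the contact described, a between-arm difference in adverse events from weeks 1 to 12 may reflect detection as well as harm.

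The size is unknown. Under the assumed gap of 90% v 50%, at true risks of 10 to 30%, false rejection runs from 16 to 50% (chi-squared) or 11 to 42% (Fisher). At 90% v 70% it is 7 to 15% or 4 to 11%. At true risks of 5% or less, Fisher stays below 5% under either gap. All of these rest on assumed risks and detection probabilities, and on every event being exposed to the gap, so events arising after week 12 would dilute the effect. If the full protocol already prescribes the same enquiry in both arms, the matter is settled by saying so.

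**What to change.** Add one identically worded adverse-event question to the activity log that both arms already keep, and ask it of everyone at the week-13 and week-25 visits. Base the between-arm comparison on events elicited this way. List events noticed only at training sessions separately and leave them out of the test. At the visits the question is best put on a form or by someone other than the blinded assessor, since an answer may reveal the allocation.

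The cost is one line on an existing form and one question at existing visits. More minor events will be recorded, and self-report by unblinded participants remains, so the change makes the opportunity to report equal but does not guarantee equal reporting. Trial status says recruitment has begun, so the earlier the change, the fewer participant-weeks lack the question.

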### Ethics

This protocol is in accordance with the Declaration of Helsinki. The study protocol and consent forms were approval by Medical Ethics Committee of the Affiliated People's Hospital, Fujian University of Traditional Chinese Medicine (approval number: 2013-021-02). Participants will sign the informed consent document prior to participation.

### Dissemination policy

Study protocol has been registered, and is available on the Chinese Trial Registry website (Registered in ChiCTR.org with the identifier ChiCTR-TRC-13003588). All participants will be the first to be informed of trail results. They will then be published in scientific journals if possible regardless of the magnitude or direction of effect. No professional writers will be employed.

